## Discussion

CIEMAR is a Europe-wide, prospective multicentre observational study of patients with colorectal liver metastases treated with microwave ablation as standard therapy. Its primary outcome measure is to evaluate local tumour control, with secondary outcome measures being overall survival, (hepatic) disease-free survival, time to progression untreatable by thermal ablation, systemic cancer therapy vacation, safety and quality of life.

The robust data of real-world, 1-year tumour control per lesion will be used to determine factors that impact the effectiveness of MWA and to identify unresectable lesions that may still be optimal for MWA, thus potentially improving the curative approach to CRLM. While the level of evidence of observational data is considered low compared to randomised controlled trials (RCTs), several comparative studies have shown that outcomes of RCTs and observational studies are comparable in terms of treatment effect and quality [22–24]. Nevertheless, a recent meta-analysis showed that the risk of bias was directly correlated with the effect estimate [25]. Therefore, the choice of a robust primary outcome measure, inclusion criteria, and prospective data collection are essential in reducing the risk of bias [26–28]. In this study, the choice of a primary outcome measure appropriate for localised treatments allows CIEMAR to precisely evaluate the extent of local tumour control with MWA and relate this to its secondary effectiveness outcome measures (26). Hence, CIEMAR will combine the strengths of the observational design with the localised effects of interventional oncological treatments and thus be able to avoid the pitfalls of observational studies that focus on more general outcome measures, such as OS or progression-free survival.

Initially, CIEMAR aimed to include 700 patients with 1050 lesions with a precision of 0.05. Unfortunately, due to the COVID-19 pandemic, some centres were understaffed or even closed, while in other cases, resources had to be re-allocated to cope with the influx of COVID-19 patients and cancer treatments, including ablation treatments, were postponed or aborted. This had a negative impact on patient enrolment. Nevertheless, the current sample size of a minimum of 803 lesions with a precision of 0.04–0.07 is statistically sufficient to evaluate the primary outcome measure.

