### Primary outcome measure

The primary outcome measure is the local control rate for all ablated tumours at 1 year (defined as fully ablated with no evidence of disease within the ablation zone at 12 months + / − 45 days after the last ablation of the respective tumour) as assessed by the investigatorsʼ routine protocols (Table 2).

**Table 2 Tab2:** Primary and secondary outcome measures

	Outcome measure	Measured according to	Definition
*Primary outcome measure*			
Effectiveness	Local tumour control at 12 months on a per lesion basis	Investigator assessment	Tumour is considered to be fully ablated with no evidence of disease within the ablation zone at 12 months + / − 45 days after the last ablation
*Secondary outcome measures*			
Safety	Adverse events	CTCAE V5.0	
Effectiveness	Overall survival	Investigator assessment	Time between the first treatment and the time of death of any cause
	Overall disease-free survival	Investigator assessment	Time between the first treatment and the time of any progression, new tumours, or death
	Hepatic disease-free survival	Investigator assessment	Time between the first treatment and the time of any progression of hepatic tumours, new hepatic tumours or death
	Time to untreatable progression by thermal ablation	Investigator assessment	Time between the first treatment and the time of progression of a treated tumour that has been determined as not treatable by thermal ablation
	Systemic cancer therapy vacation	Investigator assessment	Time between the first treatment and the start of systemic cancer therapy
	Quality of Life	EORTC QLQ-C30	

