#### Time-to-event

The first MWA treatment will be the starting point for the per-patient time-to-event analyses, and the first MWA treatment of the respective lesion for per-lesion time-to-event analyses. OS is defined as the time of death of any cause, for DFS as the time of any progression, new tumours, or death, for HDFS as the time of any progression of liver tumours, new tumours in the liver or death and for time to progression untreatable by thermal ablation as the time of progression of a treated tumour that has been determined as not treatable by thermal ablation according to the investigator. Systemic cancer therapy vacation is defined as the time between the first MWA treatment and the start of systemic cancer therapy. In these analyses, subjects lost to follow-up will be censored at the last recorded communication with the patient.

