#### Outcome measures

The median time to event and 95% confidence interval will be calculated using the Kaplan–Meier estimator. Results will be illustrated graphically using Kaplan–Meier plots and the impact of different covariates will be assessed using a stratified log-rank test and an univariable Cox proportional hazard regression. The pre-defined list of covariates can be found in Supplement 1. Covariates that have at least a 10–90% ratio and no more than 10% missing data will be used. Covariates with *p* values of < 0.1 will be included in a multivariable Cox proportional hazard regression model. Backwards elimination will be used for model building. The criteria for retaining variables in the model based on statistical significance (*p* < 0.05) and model improvement. The Cox proportional hazard assumptions will be verified and covariates that do not satisfy those assumptions will be flagged.

Quality of life outcomes will be presented by absolute values and change from baseline using summary statistics. Summaries will be broken down into subgroups and covariate analyses may be performed using analysis of covariance (ANCOVA) depending on the number of available questionnaires at the final analysis.

All statistical tests will be based on a significance level of 5%, and estimates will be presented using two-sided 95% confidence intervals. As it is not planned to test any statistical hypotheses in a confirmatory sense, statistical testing will have to be interpreted in the perspective of the study.

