#### Missing data

Missing observations will be presented as a percentage of the total. For the assessment of the primary outcome measure, a drop-out is defined as a lesion not followed up to the 12 months + / − 45 days mark. In the case of the death of a patient before the 12 months assessment, only lesions that had progressed will be regarded as not having achieved tumour control at 12 months and lesions where progression could not be determined before the death of the patient will be regarded as a drop-out. A sensitivity analysis will be done to assess potential bias due to drop-outs before the 1-year assessment. Depending on the differences between the primary analysis and the sensitivity analysis, a tipping-point analysis may be performed.

The statistical analysis will be done using R Studio version 4.4.

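### If 12-month local control is related to survival timed from the first ablation, guarantee-time bias is built in; the plan should name a landmark or time-dependent analysis

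*Protocol article*

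**What the plan says.** **Exposure.** Under Primary outcome measure, local control is per lesion and is "defined as fully ablated with no evidence of disease within the ablation zone at 12 months + / − 45 days after the last ablation" of that tumour. A lesion can be classed as controlled only if the patient is alive for that assessment.

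**Early deaths.** Missing data gives two rules for a patient who dies before the 12-month assessment. The first settles which lesions count as failures: "only lesions that had progressed will be regarded as not having achieved tumour control at 12 months". The second removes the rest from the primary analysis: "lesions where progression could not be determined before the death of the patient will be regarded as a drop-out".

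**Survival clock.** Under Time-to-event, "The first MWA treatment will be the starting point for the per-patient time-to-event analyses". Table 2 defines OS as "Time between the first treatment and the time of death of any cause". The event is given "for DFS as the time of any progression, new tumours, or death"; HDFS is the hepatic counterpart.

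**Method.** Under Outcome measures, results are shown by Kaplan–Meier and "the impact of different covariates will be assessed using a stratified log-rank test and an univariable Cox proportional hazard regression". The section shown mentions no landmark, time-dependent covariate or later time origin. The covariate list is in Supplement 1, which is not shown.

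**Intended use.** The Discussion says that the endpoint "allows CIEMAR to precisely evaluate the extent of local tumour control with MWA and relate this to its secondary effectiveness outcome measures". It presents this as a strength of the design.

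**The concern.** Control status becomes known about a year after ablation, but the survival clock starts at the first MWA. Under the article's own rules, a patient who dies early can enter the not-controlled group (if the lesion had progressed) or neither group (if it had not), but hardly ever the controlled group. Comparing OS between these groups from the first MWA therefore credits the controlled group with survival that it needed in order to be classified.

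The Limitations section names unaccounted confounding, which is a different problem. The drop-out sensitivity analysis under Missing data concerns the primary outcome, not this comparison.

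For DFS and HDFS there is a second difficulty: progression of an ablated tumour makes the lesion a failure and is also an event in the outcome.

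At stake is a statement that local control is associated with longer survival, which the data could appear to support even if no association exists.

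**Working it through.** **No plan figure to reproduce.** The article states no number for the relation between control and survival. Its sample-size figure has no bearing on this point, though it does reproduce: the full Wilson 95% width for 750 lesions at 0.8 is 0.0572, against the stated 0.057.

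**Timing.** Taking 45 days as 1.5 months, the window runs from 12 − 1.5 = 10.5 to 12 + 1.5 = 13.5 months after the lesion's last ablation. For a lesion re-ablated at month 6, the earliest assessment is 6 + 10.5 = 16.5 months after the first MWA, so re-ablation lengthens the guaranteed survival.

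**Null simulation, one lesion per patient.**
- From the article: 500 patients, control rates of 60%, 70% and 80%, the assessment window, the death and drop-out rules, and follow-up of 36 to 76 months (enrolment September 2019 to January 2023, follow-up to January 2026).
- Assumed: one-year mortality of 3% to 20%; death and local progression independent and exponential; assessment uniform over 10.5 to 13.5 months; 400 replicates per scenario.
- Progressed before assessment and before death = not controlled. Alive and unprogressed at assessment = controlled. Died unprogressed before assessment = drop-out.
- Cox model for OS on control status, first from the first MWA, then from a 13.5-month landmark in survivors. The true hazard ratio is 1.

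Hazard ratios are not controlled versus controlled. They are the reciprocals of the fitted controlled-versus-not values, e.g. 1/0.893 = 1.12 and 1/0.819 = 1.22. Ranges are over the three control rates.

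| One-year mortality | HR from first MWA | p < 0.05 | HR from landmark | p < 0.05 |
|---|---|---|---|---|
| 3% | 1.12–1.15 | 6.0–8.5% | 0.97–0.98 | 4.0–6.0% |
| 5% | 1.16 | 9.8–12.0% | 0.99 | 3.0–4.5% |
| 10% | 1.16–1.18 | 11.5–19.5% | 0.98–0.99 | 4.5–5.8% |
| 15% | 1.20–1.22 | 23.0–24.7% | 1.00–1.01 | 3.5–6.0% |
| 20% | 1.21–1.22 | 23.7–30.7% | 0.99–1.00 | 3.3–5.2% |

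The Monte Carlo standard error at 5% is √(0.05 × 0.95/400) = 1.1 points, so the inflation at 3% mortality is small. At 10% mortality, deaths before month 12 were 0.3% of the controlled group and 5.4–5.6% of the not-controlled group.

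A 90% control rate, outside the article's scenarios, was also run. With few events it was unstable: at 3% mortality the controlled-versus-not ratio was 1.03 from the first MWA and 1.25 from the landmark.

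**Null simulation, several lesions per patient.** This used 1 to 9 lesions with mean 1.95 (976/500), 80% control per lesion, and 38% five-year survival taken from the Introduction. An exponential curve gives one-year mortality of 1 − 0.38^(12/60) = 17.6%. Over 200 runs the HR was 1.21, with p < 0.05 in 30%. Over 60–90% control and 38–50% five-year survival, the HR was 1.17–1.24 with p < 0.05 in 15–34%. The 13.5-month landmark gave HR 0.98–1.01 and 2.5–7.5%.

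**Further null simulation, one-year mortality 3% to 17.6%.** From the first MWA, HR 1.11–1.23 and 8–33%. From the 13.5-month landmark, 0.96–1.01 and 4–6%.

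**DFS and HDFS.** No simulation is needed. Any progression is a DFS event and any hepatic progression an HDFS event, so progression of an ablated lesion appears on both sides of the comparison.

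**The case against.** The strongest objection is that no such analysis is specified. The sentence is in the Discussion, gives a reason for choosing the endpoint, and says what the endpoint allows. Methods never uses control status as a grouping variable for survival, and the first MWA is an unobjectionable origin for the survival outcomes themselves. A landmark is the kind of detail that a statistical analysis plan may hold, and neither that plan nor Supplement 1 is shown. The article also disclaims confirmatory testing. All this stands, and it makes the point conditional. It does not remove it: the article announces the relation and gives one per-patient origin, which does not suit it.

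Some stronger readings are tempting but not supported:
- *The controlled group can contain no death in year one.* The window opens 45 days before month 12, so a few such deaths are possible.
- *All early deaths fall in the not-controlled group.* Those without determined progression become drop-outs. Progressed patients also had to survive to progression. Both limit the bias and are in the simulations.
- *Twelve-month DFS among failures is zero by construction.* Control is timed from the last ablation and DFS from the first, and assessment may fall up to 45 days after month 12, so a failure can first appear after month 12 of DFS time. A tumour that progresses, is re-ablated and is then clear may count as controlled after causing a DFS event. The overlap is partial.
- *A 30% false-positive rate is what to expect.* It rests on a five-year survival quoted for surgery, forced through an exponential curve. Patients with life expectancy under 6 months are excluded, and early mortality may be much lower.

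**Conclusion.** The point holds conditionally. If patients are grouped by 12-month control status and OS is timed from the first MWA, the comparison favours local control when there is no link: HR about 1.1–1.2, with a false-positive rate of about 6–9% at 3% one-year mortality and about 23–33% at 17.6%. The direction is consistent across the article's control-rate scenarios, and a landmark brings both figures back close to nominal. The size depends mainly on one-year mortality, which is assumed, and also on exponential times, on independence of progression and death, and on how lesions are mapped to patients, for which the article gives no rule. The documents do not show that the sponsor has chosen the biased analysis. This is a secondary, non-confirmatory analysis, but one that the article puts forward as a benefit of its primary outcome, so it should be settled before reporting.

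**What to change.** Add to Time-to-event and Outcome measures that any analysis relating local control to OS uses one of two approaches, with a stated rule for turning lesion status into patient status:
1. A landmark after the assessment window (12 months + 45 days, later where lesions are re-ablated or treated in stages), in patients alive and classified then, with time counted from the landmark.
2. First local failure as a time-dependent covariate from the first MWA. This handles staged and repeat ablation more easily.

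For DFS and HDFS, relate control only to new disease other than the local failure itself, or report the overlap with the result.

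The cost is wording; no new data are needed. The landmark drops patients who die or leave before it from this one analysis. Deaths alone by 13.5 months would be 1 − 0.97^(13.5/12) = 3.4% at 3% one-year mortality, and 1 − 0.38^(13.5/60) = 19.6% under the 38% five-year assumption. The time-dependent version keeps these patients.

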**Methods:**

Eligible patients are adults with up to 9 local treatment naïve CRLM of ≤ 3 cm completely treatable with either MWA alone or MWA with resection and/or radiotherapy within 8 weeks. Data are collected, at baseline, every 3 months until 12 months, and thereafter every 6 months until the end of the study. The primary outcome measure is local tumour control. Secondary outcome measures are overall survival, (hepatic-) disease-free survival, time-to-progression untreatable by ablation, systemic therapy vacation, safety, and quality of life. Covariates related to the primary outcome measure will be assessed using a stratified log-rank test and an univariable Cox proportional hazard regression. A sample size of 500 patients with 750 lesions produces a two-sided 95% confidence interval with a precision equal to 0.057.

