### Statistical analysis

#### Sample size calculation

As the total number of available lesions will depend on how many lesions per patient are treated, several scenarios were used to calculate the required sample size to achieve sufficient precision for analysis. Based on previously published data [11, 16], local tumour control rates of 60%, 70%, and 80% for 1, 1.5, and 2 tumours per patient were chosen as possible scenarios. Using the resulting sample size, the expected precisions were calculated using the two-sided 95% confidence interval according to the Wilson score method [20, 21].

A sample size of 500 patients with a median of 1.5 tumours per patient produces a two-sided 95% confidence interval with a precision equal to 0.057 when the sample proportion is 0.8.

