## Current status of the study

Between October 2018 and June 2022, 100 hospitals that met the selection criteria were invited, of which 36 were activated (by means of training, access to the database, and eligibility to include patients). As of January 2023, 500 patients have been enrolled with 976 treated tumours, achieving the minimum sample size of 976 lesions for a precision between 0.04 and 0.06. Follow-up data will be collected until January 2026. The final clinical outcome results are expected to be published by 2027.

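### The precision ranges for 803 and 976 lesions start at 0.04, which the stated method and the 60/70/80% control rates do not give; the upper ends are correct

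*Protocol article*

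**What the plan says.** Under Sample size calculation, the article states its scenarios: "local tumour control rates of 60%, 70%, and 80% for 1, 1.5, and 2 tumours per patient were chosen as possible scenarios". It names the method: "the expected precisions were calculated using the two-sided 95% confidence interval according to the Wilson score method". It gives one worked result, for 500 patients with 1.5 tumours each, which "produces a two-sided 95% confidence interval with a precision equal to 0.057 when the sample proportion is 0.8".

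Three other places report precision:

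- Abstract, Methods: "A sample size of 500 patients with 750 lesions produces a two-sided 95% confidence interval with a precision equal to 0.057", with no control rate attached.
- Current status of the study: 976 treated tumours, "achieving the minimum sample size of 976 lesions for a precision between 0.04 and 0.06".
- Discussion: "Initially, CIEMAR aimed to include 700 patients with 1050 lesions with a precision of 0.05". After explaining the shortfall in recruitment, the same paragraph says that "the current sample size of a minimum of 803 lesions with a precision of 0.04–0.07 is statistically sufficient".

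Neither of the last two sections names the control rates behind its range.

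**The concern.** The article prints its method, its assumed rates and its results, so the results can be checked against the inputs. The lower end of both ranges, 0.04, is narrower than anything the listed rates produce at those lesion counts.

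The figure matters because the 0.04–0.07 range stands in the sentence that defends recruiting 500 patients instead of 700, shortly after the original 0.05 is mentioned. A lower end of 0.04 makes the retained precision look better than the stated scenarios allow. The interval width is also the only design justification given for the primary outcome.

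Two smaller inconsistencies sit in the same statements. Current status calls 976 lesions the minimum and the Discussion calls 803 the minimum, while the one worked figure uses 750. The Abstract gives 0.057 without the 80% condition that the sample size section attaches to it.

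**Working it through.** **Inputs.** Two-sided 95% Wilson interval, z = 1.96; control rates p = 0.60, 0.70, 0.80; worked figure 0.057 at p = 0.8 for 500 × 1.5 = 750 lesions (all from Sample size calculation). Lesion counts: 976 (Current status), 803 and 1050 (Discussion).

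**Formula.** Full width of the Wilson interval:

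W = 2z·√[p(1−p)/n + z²/(4n²)] / (1 + z²/n)

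**Step 1: reproduce the plan's figure.** For n = 750, p = 0.8:

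- p(1−p)/n = 0.16/750 = 0.00021333
- z²/(4n²) = 3.8415/2,250,000 = 0.00000171
- square root of the sum = 0.014664; times 3.92 = 0.05748
- divided by 1 + 3.8415/750 = 1.00512, W = 0.0572

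This matches 0.057. The half-width is 0.029 and does not match, so precision here means full width. The original 0.05 also reproduces by rounding: n = 1050, p = 0.8 gives 0.0483.

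**Step 2: apply the same formula to the reported counts.**

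| Lesions | 60% | 70% | 80% | Printed range | 90% (not listed) |
|---|---|---|---|---|---|
| 750 | 0.0700 | 0.0655 | 0.0572 | 0.057 | 0.0430 |
| 803 | 0.0676 | 0.0633 | 0.0553 | 0.04–0.07 | 0.0416 |
| 976 | 0.0614 | 0.0574 | 0.0501 | 0.04–0.06 | 0.0377 |
| 1050 | 0.0592 | 0.0554 | 0.0483 | 0.05 | 0.0363 |

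The upper ends, 0.07 and 0.06, are the 60% column rounded. The lower ends are not the 80% column: 0.0553 and 0.0501 do not become 0.04 by rounding or by truncation.

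**Step 3: look for another route to 0.04.**

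- Other 95% formulas at 80% control: continuity-corrected Wilson gives 0.0565 (803) and 0.0512 (976); Wald gives 0.0553 and 0.0502.
- Half-widths over 60–80% are 0.028–0.034 (803) and 0.025–0.031 (976), which fit neither end.
- The most favourable listed combination, 500 patients × 2 tumours = 1000 lesions at 80%, gives 0.0495.
- At 80% control, a width of 0.040 needs about 1,535 lesions. A width below 0.045, which would round to 0.04, needs about 1,213.
- Holding the lesion count fixed, a width of 0.040 needs p ≈ 0.908 (803) or 0.885 (976). A width below 0.045 needs p above about 0.880 or 0.848.

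**Step 4: size of the discrepancy at 80% control.** 0.0553 − 0.04 ≈ 0.015 at 803 lesions and 0.0501 − 0.04 ≈ 0.010 at 976. If the printed 0.04 is taken to cover anything up to 0.045, the excess is 0.010 and 0.005.

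**The case against.** The strongest reply is that the arithmetic may be right and only a scenario is missing. Neither section says that its range covers 60–80% alone. Over 60–90%, all four printed ends reproduce by rounding: 0.0676 to 0.0416 at 803 lesions and 0.0614 to 0.0377 at 976. The article is condensed and the full protocol may list a 90% rate. This stands as a plausible explanation, but it does not remove the inconsistency: the article lists three rates, 90% is not among them, and no reader can tell that 0.04 depends on it.

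A reader might infer that the sufficiency statement rests on 0.04 and therefore fails. The documents do not support that. A precision range is judged at its wide end, and the wide ends are correct. Nothing in the article makes 0.04 or 0.05 a threshold, and no confirmatory testing is planned. At 80% control both counts do better than the 0.057 design figure (0.055 and 0.050).

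A reader might also infer that the original 0.05 has been lost, or that only 976 lesions can reach it. Neither follows. Among the listed rates, the original 1050 lesions reached 0.05 only at 80% (0.059, 0.055, 0.048), and 976 lesions match it there to two decimals. At 803 lesions, a width of 0.05 is reached from about 84.5% control.

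On the smaller points, the missing 80% condition in the Abstract is condensation, since the sample size section states it. The 750 is one of several tumours-per-patient scenarios and not a unique minimum. Both are matters of clarity.

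**Conclusion.** The point holds as a reporting error in a design figure. On the stated method and control rates, the lower end of 0.04 is not obtained at either lesion count. The full widths are 0.055–0.068 at 803 lesions and 0.050–0.061 at 976. Either the best-case precision is overstated by 0.015 and 0.010 (0.010 and 0.005 after allowing for rounding), or it depends on a control rate near 90% that the article does not list. In full width these are small amounts, and half as much on each side of the estimate. The upper ends, the 0.057 figure and the sufficiency statement are not overturned. The two counts described as a minimum, 803 and 976, do contradict each other.

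All widths here follow the plan in treating lesions as independent and every lesion as assessed at 12 months. Correlation between lesions in one patient would move them further from 0.04. As an illustration only, take the design effect 1 + (lesions per patient − 1) × correlation, with 803/500 = 1.606 or 976/500 = 1.952 lesions per patient. Assumed correlations of 0.05 to 0.3, which the documents do not give, then produce about 0.056–0.074 and 0.051–0.070. The finding does not depend on this.

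**What to change.** 1. In Current status of the study and in the Discussion, restate the ranges as full 95% interval widths over 60–80% control: 0.050–0.061 for 976 lesions and 0.055–0.068 for 803. Alternatively, if a 90% rate was used, add it to Sample size calculation and say that 0.04 holds only there (0.038 at 976 lesions, 0.042 at 803).
2. Explain or reconcile the two minimum lesion counts, 803 and 976, and say how they relate to the 750 behind the 0.057.
3. In the Abstract, attach the 80% control condition to 0.057. At the same 750 lesions the width is 0.066 at 70% and 0.070 at 60%.

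The sufficiency statement can stay. The cost is a text correction, and with the first option the stated best case becomes somewhat less favourable. Enrolment, follow-up and analysis do not change.
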